#### Iterative Feedback

Throughout phases 2 and 3 of the study, feedback will be iteratively requested from community members through semistructured qualitative interviews and advisory committee meetings.

In addition to obtaining feedback about initial adaptations to the UP-A, feedback will also be requested at the end of phase 2 by individuals who participated in the study. These interviewees may consist of caregivers, students, and mental health care providers. Participants in the U-PEACE pilot case series will be asked to reflect on their experiences in the program and provide feedback on (1) how the program impacted them, (2) how fitting the program was for them and members of their community, and (3) whether the logistics of the program were feasible. On the basis of phase 2 feedback, the research team will adapt the content and delivery of U-PEACE for implementation during the RCT phase of the study. This second iteration of adaptations will again be focused on improving the cultural acceptability of content and increasing logistical feasibility of delivery at the participating Title 1 high schools.

Some participants and their caregivers who are randomized to the U-PEACE group during the RCT phase (phase 3) of the study will be randomly selected to participate in semistructured qualitative interviews at the end of their participation in the program (for a sample interview guide, refer to Multimedia Appendix 3). Participants will consist of an even distribution of responders and nonresponders to the U-PEACE program. Interview questions will mirror questions asked of the pilot case series participants. The third iteration of adaptations will have the same focus as the previous adaptations, with an added focus of making the program scalable and deliverable in similar Title 1 high school settings. The RCT feedback (following completion of phase 3) may also provide guidance on how to further scale the implementation and delivery of U-PEACE in other high school settings.

In addition to qualitative interviews, the research team will also ask the Title 1 high school communities to identify members who are well-known on their campuses and engaged in the community to participate in an advisory committee. Members will ideally include teachers, students, caregivers, school mental health providers, and administrators from each of the high schools. Members will meet at the end of each of the first 3 study aims. During the advisory committee meetings, members will be updated on the study’s status and asked to provide feedback. Community members that participate in qualitative feedback interviews or advisory committee meetings will receive US $50 compensation for each time they participate in providing feedback.

### Prevention Program Content and Delivery

#### Content

The resulting U-PEACE indicated prevention program is anticipated to maintain the same overarching intervention principles and flexible modules as the UP-A. Content within existing UP-A modules may be adapted (eg, examples of skills may be more tailored to reflect common adolescent experiences in Title 1 high schools), and modules may be added or removed based on community member feedback. Like the UP-A, each module will have corresponding session materials that facilitate content learning and encourage practice of skills outside of the U-PEACE group. In addition to clinician, adolescent, and caregiver materials; we also anticipate materials to be created for school community members (eg, teachers, school mental health providers, or counselors) who may be involved in facilitating adolescents’ practice of skills or homework completion.

#### Study Intervention

Given that the study was already in phase 3 when this manuscript was submitted for publication, the written protocol for U-PEACE delivery will incorporate community member feedback from phases 1 and 2. For a CONSORT diagram of the RCT, refer to Figure 2.

**Figure 2 figure2:**
[figure not shown]
Anticipated CONSORT (Consolidated Standards of Reporting Trials) diagram for the Unified Protocol for Transdiagnostic Treatment of Emotional and Academic Challenges in Education (U-PEACE) study. The diagram includes information from the anticipated participant allocation. At the completion of the study, a final CONSORT diagram will be presented with study results that include final data regarding recruitment and retention of participants. SAU: service as usual.

While the research team will be exploring the feasibility of telehealth-delivered U-PEACE, most U-PEACE sessions are expected to be delivered in person, during lunchtime, and in group format. Students who are enrolled in U-PEACE will be permitted to access additional primary, medical, and mental health care services within the school clinics throughout their participation in U-PEACE. The original UP-A typically takes place over 12 to 16 sessions. Thus, it was anticipated that U-PEACE would eventually contain a session count in this range. Each U-PEACE group will ideally have approximately 4 to 8 students enrolled in it at one time, as well as 1 to 2 clinicians in training who serve as program leaders for the group. At the beginning of the U-PEACE group, adolescent participants will receive a binder of U-PEACE session and homework worksheets that they can reference when learning and reviewing the program content. Adolescents will be expected to bring their binders to every U-PEACE session and practice skills learned in the group as homework between program sessions. In addition to U-PEACE binders, adolescents will also be given a caregiver session summary sheet to provide to their caregivers; these summary sheets are intended to keep caregivers informed about skills their adolescents are learning in U-PEACE.

Although initial community member feedback suggested that the research team bring external clinicians into the schools to deliver U-PEACE, the team decided to also incorporate nonclinic school staff into the delivery of U-PEACE by adding coaches to the program. Coaches were typically existent school counselors or school mental health providers at the target schools who are intended to function in U-PEACE in a similar manner to how caregivers function in the UP-A: their primary role is to review and practice skills learned in U-PEACE sessions with adolescents outside of the program (eg, ensuring homework completion). Coaches will try to meet with each assigned student one time per week for approximately 15 minutes. During the meeting, coaches will briefly check in with students regarding whether they have been able to practice the skills they learned in session. They will also provide students with session summary materials if they cannot attend the previous session.

#### Comparison Condition

Individuals assigned to the comparison condition will have access to any medical, social work, and psychotherapy services available through the school clinic to address emotional and behavioral concerns determined to be needed during the intervention period. The school clinic services are available in person or via telehealth throughout the year. A study staff member will also meet with all SAU adolescents for approximately 10 minutes per week (via telehealth as needed) for 13 weeks to complete weekly study measures, assess and provide linkage to clinic services requested or needed, and monitor for clinical deterioration. If an adolescent seems to be deteriorating in any significant way, additional mental health services or appropriate referrals will be offered after consultation. Data will also be collected from SAU participants 1-month after completion of the 13 weekly meetings. After the 1-month follow-up, SAU participants may be offered participation in the U-PEACE program via telehealth or in person.

SAUs vary in frequency and type based on the availability of the school clinic providers. These services may include weekly individual or group CBT, case management, and psychological and psychiatric consultations. These services are often provided by nurses, primary care physicians, master’s-level therapists, social workers, psychologists, or psychiatrists. The receipt of these services within the school clinic will be monitored and reported. If a higher level of care is needed than what is typically provided through the school clinic, patients are referred to community resources. Participants will also be asked to report on their access and use of emotional and behavioral health services outside of the school clinic.

### Measures

#### Overview

Each U-PEACE and SAU group will have 4 assessment time points (baseline, midpoint, after completion, and 1-month follow-up) of questionnaire administration. Detailed information regarding questionnaire administration at each time point can be found in Table 2.

**Table 2 table2:** List of assessment measures and time points.

Measure name	Every session	Baseline	Midpoint	After completion	1-month follow-up
Demographic survey	N/A^a^	Adolescent and parent or caregiver	N/A	N/A	N/A
DIAMOND-KID^b^–full interview [65]	N/A	Adolescent	N/A	N/A	N/A
DIAMOND-KID–initial interview [65]	N/A	Adolescent^c^	N/A	N/A	N/A
DIAMOND-KID–self-report scanner [65]	N/A	Adolescent^d^	Adolescent^d^	Adolescent^d^	Adolescent^d^
Service Utilization Form	N/A	Adolescent^d^	Adolescent^d^	Adolescent^d^	Adolescent^d^
Generalized Anxiety Disorder 7-item Scale [61]	N/A	Adolescent and parent or caregiver	Adolescent and parent or caregiver	Adolescent and parent or caregiver	Adolescent and parent or caregiver
Child Anxiety Interference Scale–Academic Subscale [66,67]	N/A	Adolescent and parent or caregiver	Adolescent and parent or caregiver	Adolescent and parent or caregiver	Adolescent and parent or caregiver
Patient Health Questionnaire-9 [59]	N/A	Adolescent and parent or caregiver	Adolescent and parent or caregiver	Adolescent and parent or caregiver	Adolescent^e^ and parent or caregiver
Affective Reactivity Index [68]	N/A	Adolescent and parent or caregiver	Adolescent and parent or caregiver	Adolescent and parent or caregiver	Adolescent and parent or caregiver
Adolescent Academic Problems Checklist [69]	N/A	Teacher	Teacher	Teacher	Teacher
The Revised Children’s Anxiety and Depression Scale–Short-Form [70]	N/A	Adolescent^d^	Adolescent^d^	Adolescent^d^	Adolescent^d^
Behavior and Feelings Survey [71]	N/A	Adolescent^d^	Adolescent^d^	Adolescent^d^	Adolescent^d^
School achievement (as measured by attendance and report card)	N/A	Adolescent^d^	N/A	Adolescent^d^	Adolescent^d^
Everyday Discrimination Scale [72]	N/A	Adolescent	Adolescent	Adolescent	Adolescent
Abbreviated Multidimensional Acculturation Scale [73]	N/A	Adolescent	Adolescent^c^	Adolescent^c^	Adolescent^c^
Distress Tolerance Scale [74]	N/A	Adolescent	Adolescent	Adolescent	Adolescent
Top problems [75]	Adolescent	Adolescent	Adolescent	Adolescent	Adolescent
Participant adherence	Clinician	N/A	N/A	N/A	N/A
Therapeutic Alliance Scale for Children–Revised [76,77]	N/A	N/A	Adolescent	N/A	N/A
Client Satisfaction Questionnaire [78]	N/A	N/A	Adolescent	N/A	N/A

^a^N/A: not applicable.

^b^DIAMOND-KID: Diagnostic Interview for Anxiety, Mood, and OCD-Related Neuropsychiatric Disorders: Child and Adolescent Version—Full Interview.

^c^Not administered at these time points in the randomized controlled trial.

^d^Measure was only administered during the randomized controlled trial.

^e^Patient Health Questionnaire-8 was used at 1 month.

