#### Anxiety and Depression Symptoms

Adolescents’ anxiety symptoms will be measured using the Generalized Anxiety Disorder 7-item Scale (GAD-7) [61]. The GAD-7 will be used as both a self- and caregiver-report measure; the items in it are rated on a 4-point Likert-type scale that ranges from “not at all” to “nearly every day,” with higher scores suggesting more severe anxiety symptoms. While the authors are not aware of published psychometric properties on the parent-report GAD-7, the self-report GAD-7 has demonstrated good reliability in adolescent populations (Cronbach α=0.88) and has demonstrated strict measurement invariance by adolescents’ sex and grade, as well as good convergent and discriminant validity [62,79].

Adolescents’ depression symptoms will be measured using the PHQ-9 [59]. Items on the PHQ-9 scale are rated on a 4-point Likert-type scale that ranges from “not at all” to “nearly every day,” with higher scores suggesting more severe depression symptoms. The PHQ-9 has demonstrated good internal reliability (McDonald Ω=0.87) among adolescents, and confirmatory factor analysis for a 1D model suggested adequate fit [80].

There may be instances in which the research team chooses to administer a modified version of the PHQ-9 to adolescents and their caregivers. For instance, given that this measure may be administered remotely without the presence of a study team member, the Patient Health Questionnaire-8 (PHQ-8) may be used to ensure that any suicide-related concerns are handled immediately and in person by the research team [60]. Research has suggested that omitting the suicide item on the PHQ-9 has minimal impact on scoring [81]. The correlation between the PHQ-9 and PHQ-8 remains high; therefore, the cutoff scores remain unchanged [60,81]. While the authors are not aware of published psychometrics for parent-report PHQ-8, research on the general population suggests good sensitivity and specificity [60].

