#### Quantitative Analyses

Quantitative analyses will be conducted to assess (1) within-participant treatment-related changes in emotion regulation and symptoms after participation in U-PEACE and (2) implementation outcomes, including treatment fidelity, acceptability, and implementation costs. We will examine missing data patterns, attrition rates, and distributional properties of measures and use transformations when necessary. Depending on patterns of missing data, analyses may use full maximum likelihood estimation, multiple imputation, and inclusion of covariates related to missingness to account for missing data.

Reliable change indices (RCIs) will be calculated by dividing the within-respondent differences in self-report and caregiver scores (ie, anxiety symptoms, depression symptoms, irritability, anxiety-related impairment, and academic problems) from baseline to after treatment by the SE for each measure [92]. RCI has previously yielded reliable estimates of clinically significant change over the course of treatment and can successfully analyze small sample sizes [93]. RCI >1.96 indicates clinically significant change throughout the course of the program—which would provide preliminary support that U-PEACE is impacting theoretical mechanisms and participants’ outcomes.

Furthermore, multilevel models will be evaluated to consider nesting of repeated measures (3 or 4 time points, depending on the measure) within participants, who are further nested within study conditions. School and U-PEACE group provider or providers will be included as predictors of intercept and slope to control for environmental differences between the groups. The best-fitting model for change over time will be determined for each dependent variable based on the Akaike Information Criterion and Bayesian Information Criterion. Time will be coded in weeks and will be “centered” alternately at treatment follow-up, such that model intercepts will represent mean scores at these assessments [94]. Treatment condition (ie, U-PEACE or SAU) will be entered as a predictor of the level 2 growth curve parameters (intercepts and slopes). These models will be used to assess group differences in both purported mechanisms of change (ie, emotion regulation measures) and in program outcomes (ie, symptom measures, academic outcomes, and diagnostic measures) as evidenced by slope or mean level differences at different time points.

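### Adolescent depression moves from the PHQ-9 to the shorter PHQ-8 at the 1-month visit with no common scoring stated, which tilts within-arm growth curves slightly toward improvement

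*Protocol article*

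**What the plan says.** The Anxiety and Depression Symptoms section names the instrument: "depression symptoms will be measured using the PHQ-9". Table 2 lists it at baseline, midpoint, after completion and 1 month. The 1-month cell reads "Adolescent^e^ and parent or caregiver", and footnote e explains that "Patient Health Questionnaire-8 was used at 1 month". The footnote mark sits on the adolescent entry only.

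The same section leaves room for further substitution: "There may be instances in which the research team chooses to administer a modified version of the PHQ-9 to adolescents and their caregivers". The reason given is that the form may be completed remotely with no team member present. Two statements support treating the forms alike: "Research has suggested that omitting the suicide item on the PHQ-9 has minimal impact on scoring", and "The correlation between the PHQ-9 and PHQ-8 remains high; therefore, the cutoff scores remain unchanged".

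Under Quantitative Analyses, growth models are fitted to three or four time points depending on the measure (four for the PHQ). Time is centred at treatment follow-up, "such that model intercepts will represent mean scores at these assessments". The reliable change index (RCI) is computed from baseline to after treatment. Growth parameters are then set against cutoffs and RCIs to sort students into four outcome categories, which are used for reporting to stakeholders and for choosing interviewees. The article does not mention scoring the common items at every visit, prorating the shorter form, or leaving the 1-month score out.

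**The concern.** A change model depends on levels. A high correlation between two forms says that they rank students similarly; it does not say that a student with unchanged symptoms gets the same total on both. An unchanged cutoff addresses classification at a single visit, not the slope of a series whose last point is on a shorter scale.

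The direction of the error is known. Item 9 cannot score below zero, so omitting it only at the end can make a student look better and never worse. In the adolescent series the change of form coincides with the last time point, so the model cannot separate the two. What is at stake is the reported within-arm improvement in depression, the estimated mean at follow-up, and the labels derived from the fitted curves.

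**Working it through.** The article gives no figure for this effect. Its power statement does not bear on it.

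**Inputs from the article**
- Form by visit (adolescent): PHQ-9, PHQ-9, PHQ-9, PHQ-8 (Table 2, footnote e).
- Item format: "Items on the PHQ-9 scale are rated on a 4-point Likert-type scale".
- Intercept location: treatment follow-up (Quantitative Analyses).
- Length of the intervention period: 13 weekly contacts (Comparison Condition).

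**Assumptions, not in the article**
- Items coded 0-3.
- Visits at weeks 0, 6.5, 13 and 13 + 52/12 = 17.33.
- Mean item-9 score at 1 month, *m*, between 0.1 and 1.0.
- A straight line fitted to complete arm means. A multilevel model with missing data would differ somewhat, and it shrinks individual estimates.

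**Step 1, range.** Nine items give a maximum of 9 × 3 = 27, eight give 8 × 3 = 24. Omitting item 9 removes 0 to 3 points per person.

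**Step 2, leverage of the last visit.** The mean week is 36.83/4 = 9.21. The deviations are −9.21, −2.71, 3.79 and 8.125, and their squares sum to 172.5. Lowering only the last point by *m* changes:
- the slope by −*m* × 8.125/172.5 = −0.047*m* per week;
- the fitted value at 1 month by −*m* × (1/4 + 8.125²/172.5) = −0.633*m*;
- the fitted value at post by −*m* × (1/4 + 8.125 × 3.79/172.5) = −0.43*m*.

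**Step 3, within-arm size**

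| Assumed item-9 mean | Shift in 1-month intercept (points) | Shift in slope (points per week) |
|---|---|---|
| 0.1 | −0.06 | −0.005 |
| 0.3 | −0.19 | −0.014 |
| 0.5 | −0.32 | −0.024 |
| 1.0 | −0.63 | −0.047 |

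With a quadratic curve the 1-month intercept moves by 0.894*m*, that is 0.09 to 0.89 points. For an assumed PHQ SD of 5 to 6, the linear shifts run from 0.06/6 = 0.01 SD to 0.63/5 = 0.13 SD.

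**Step 4, one student.** A student who scores 3 on item 9 throughout and does not change has a fitted 1-month value 0.633 × 3 = 1.9 points too low on an individual straight line, before shrinkage.

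**Step 5, arm contrast.** The scheduled switch is the same in both arms, so the contrast moves by 0.633 times the arm difference in item 9. That is 0 if the arms are equal and 0.06 to 0.32 points for a difference of 0.1 to 0.5. The move reduces the apparent benefit of whichever arm has the lower item-9 score.

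**Step 6, with common items.** If items 1-8 are summed at every visit, every term above is zero.

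**The case against.** The article discloses the substitution, gives a safety reason for it, and cites sources for minimal impact and unchanged cutoffs that cannot be examined here. That answers much of any complaint about cutoffs at a single visit. It does not answer the trajectory point, because neither statement is about equality of mean level over time.

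It can be said that the article never states that raw totals will be pooled, and that scoring detail belongs in an analysis plan. This is fair as to detail. But the article does take a position: it changes the form at a fixed visit and treats the scores as interchangeable. The result in Working therefore applies if the totals are used as described.

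Several stronger readings are tempting and do not hold:
- **That the RCI is corrupted.** A reader might set the possible 2 to 3 point loss against a reliable-change threshold. The RCI window ends at post, and Table 2 lists the PHQ-9 at both ends. Only an unscheduled remote substitution could reach it.
- **That the randomised comparison is biased.** Both arms share the schedule and the footnote. The telehealth wording under Comparison Condition concerns weekly contacts, at which Table 2 does not schedule the PHQ, and telehealth is also being explored for U-PEACE. Nothing shows that remote PHQ use differs by arm.
- **That caregiver scores switch form too.** The footnote covers adolescents only. For caregivers the text permits a modified form but fixes no switch.
- **That all results rest on the 1-month intercept.** The centring sentence refers to assessments in the plural, so 1 month need not be the only intercept reported. At post the shift is 0.43*m* instead of 0.633*m*.

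Two further points stand. Students with symptoms judged too severe are excluded (Recruitment), which makes high item-9 means less likely. The RCADS-SF is scheduled at all four RCT visits with no stated change of form, so depression is not measured by the PHQ alone.

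**Conclusion.** The point holds in a limited form. The adolescent PHQ series uses two totals, the shorter one falls at the last visit, and the stated justification does not make them comparable in a growth model. The within-arm trajectory and the follow-up intercept are pushed toward improvement by about 0.06 to 0.63 points under a linear fit, and the categories derived from growth parameters inherit that push. The direction is certain wherever item 9 would have been endorsed. The size rests on assumed item-9 means, visit weeks and item coding, and is small on average. The documents do not support a claim that the arm contrast or the baseline-to-post RCI is biased by the scheduled switch. This is a modest, one-directional artefact that should be removed because removal is nearly free.

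**What to change.** State that the depression score in the growth models, and in the outcome categories derived from them, is the sum of PHQ items 1-8 at every visit. Apply the same eight-item score to the RCI and to the caregiver series wherever a PHQ-8 was substituted, and record which form was given at each assessment. Keep the nine-item total for eligibility and as a sensitivity analysis through post, and report item 9 separately at the visits where it was collected.

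This is rescoring only. It needs item-level data but no new collection, and it leaves the way the form is administered and safety concerns are handled as planned. The downside is that the suicide item no longer contributes to the longitudinal total, which is why it should be reported on its own.
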